##### Diary of medical costs

As patients are allowed to seek medical help outside the participating hospital between the 1 month and 3 months follow-up visits, healthcare/medication use cannot be monitored using the hospital’s financial records. Therefore, patients will be handed a diary in which they should collect all information regarding tinnitus related medical help, such as physician consultations (including general practitioners), psychological consultations, medication use and treatments in the context of their tinnitus complaints.

### Ethics

Every patient will impart written consent for participation. The study protocol and the use of the developed smartphone application received a consolidated positive advice by the Belgian Federal Agency for Medicine and Health Products (FAMHP) and an independent Ethical Committee (Ref. CIV-BE-21-09-037760). The study protocol was registered at Clinicaltrials.gov (ref. NCT05245318).

### Intervention

#### Standard clinical care (control treatment)

The standard care treatment comprises 12 face-to-face individual physiotherapy sessions at a ratio of 1 session of 30 min a week [14, 37]. Every patient in the control group will be treated in a tailored manner according to their results on the baseline measurements and will thus receive a personalised 12-week treatment program. The multimodal treatment program will consist of exercises to increase strength, endurance and coordination of the cervical spine (deep neck flexors and extensor muscles) and shoulder stabilising muscles, exercises to increase mobility and improve posture [14, 15]. In case of jaw complaints, stretching exercises of the masticatory muscles to increase jaw mobility are added to the program [15, 19]. In addition, manual mobilisations can be performed if limitations in the mobility of the neck or temporomandibular joints are observed. In the same manner, manual techniques to decrease muscle tension in neck and jaw muscles can be added to the exercise program [14, 15, 19]. Additionally, patients receive counselling to learn about their neck/jaw complaints and to guide them to good posture and movement habits, such as emphasising the importance to change posture when sedentary and specific advice concerning mouth habits and sleep hygiene in patients with jaw complains [15]. Patients will be motivated to perform the exercise program at home on a daily basis but will not receive additional support on the home exercises between sessions. The patient’s performance on the exercises will be evaluated during the weekly session in the clinic. Patients in the control group will not receive any tinnitus counselling.

#### Blended physiotherapy program (experimental treatment)

The experimental group will receive a blended physiotherapy program consisting of only six instead of twelve physiotherapy treatments over a period of 12 weeks, meaning one treatment session of 30 min every 2 weeks. In addition, a smartphone application will offer the patients a daily exercise program, based upon the standard physiotherapy treatment for ST [14–22], and psychological tinnitus counselling. This tinnitus counselling program consists of two sessions a week and is developed by psychologists of the University of Regensburg [64, 65]. Before the start of the program, the exercises will be tailored to the area, type and degree of the patient’s dysfunctions. During the six physiotherapy treatment sessions, patients will, if needed, receive manual mobilisations to increase mobility of the neck and/or temporomandibular joints or manual techniques to decrease muscle tension in neck and jaw muscles [14–22]. Additional counselling on knowledge about neck and jaw pain and advice about posture and movement habits will also be provided by the physiotherapist during these six treatment sessions.

#### Post-trial care

Patients of both intervention groups will be followed up by the multidisciplinary team of the University Hospital of Antwerp after the study trajectory and if requested by the patient post-trial care will be provided when necessary.

### Sample size and power

The study is designed as a non-inferiority trial of a continuous response variable comparing independent control and experimental subjects. The primary outcome is the change in TFI from baseline to 1-month follow-up. We hypothesise that there is no significant difference between the control and experimental group for this outcome. A non-inferiority margin is chosen at 6.5 points, being half of the minimally clinically important difference [66]. Assuming a standard deviation of 20 points (SD found in international literature [67] as well as in previous performed own studies [14, 18]) and a significance level (*α*) of 0.025, an achieved sample size of 150 patients per group is required to have 80% power to show non-inferiority using a one-sided, independent samples *t*-test. Considering a possible 10% drop-out, based on previous studies in ST [14, 37], 167 patients will be recruited into each group. Hence, a total of 334 patients will be recruited for the study.

### Data analysis and statistics

#### Effectiveness analysis

##### Primary analysis

Our primary hypothesis is that the change in TFI-score from baseline to 1-month follow-up will be non-inferior in the experimental group compared to the control group. After calculating a TFI-change score from baseline to 1-month follow-up, a two-sided 95% confidence interval for the mean difference in this change score between experimental and control group will be compared to the non-inferiority margin of 6.5.

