### Outcome measures

The following outcome measures will be collected at baseline and during the two follow-up visits. The first follow-up visit is planned 1 month (range: 4 to 7 weeks) after the last treatment session. The second follow-up visit will take place 3 months (range: 8 to 13 weeks) after the last treatment session. In between the first and second follow-up moment should be a minimum period of 4 weeks. For certain outcome measures additional measuring moments are planned, these are specified individually below. See Fig. 2 for an in-detail schedule of enrolment, interventions and assessments in accordance with the SPIRIT 2013 guidelines [30].

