#### Primary outcome measure

The primary outcome is the change in Tinnitus Functional Index (TFI) score from baseline to 1 month after the treatment. This time point was chosen since previous research indicated that the largest treatment effect on TFI is to be expected 1 month after the last treatment session [37–40]. For the cost-effectiveness analysis, an additional time point, immediately after the last treatment session, is added to be able to link the amount of decrease on TFI to the EuroQoL (EQ)-5D-5L that assesses HRQOL. The TFI is a self-report questionnaire comprising 25 questions, each scored on an eleven-point Likert scale, objectifying the impact and severity of tinnitus. Eight subscores are differentiated, namely intrusiveness, sense of control, cognitive complaints, sleep disturbance, auditory difficulties, relaxation, quality of life (QOL) and emotional distress. The total score and subscores will be noted on a scale of 0 to 100 with higher scores indicating higher levels of tinnitus-related distress [33, 34]. A change of 13 points out of 100 is considered a clinically relevant change [33]. TFI has a high sensitivity to change, a good test-retest reliability (*r*: 0.78), discriminant validity with the Beck Depression Inventory-Primary Care (*r*: 0.56) and convergent validity with both the Tinnitus Handicap Inventory (THI) (*r*: 0.86) and the visual analogue scale (VAS) for tinnitus loudness (*r*: 0.75) [33, 41, 42].

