##### Secondary analysis

The continuous secondary outcomes and baseline characteristics, measured at the different time points, will be used in a linear mixed model allowing correction for repeated measurements from the same patient to compare their profiles over time and identify at which time points the groups differ. Other variables such as age, gender and tinnitus grade can also be included in these models.

Considering this is a non-inferiority trial, primary and secondary endpoints are analysed in first instance in the per-protocol population. The per-protocol population are all eligible patients who adhered to the complete protocol. The intention-to-treat population will be taken into consideration in a sensitivity analysis afterwards.

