## Discussion

The aim of this study is twofold, namely investigating the effectiveness and cost-effectiveness of a blended physiotherapy program for ST, including a smartphone application designed to increase therapy compliance and provide tinnitus counselling.

The study population in scope are adult ST patients. Patients will be diagnosed with ST by a multidisciplinary team of specialists in their field. This team will exist of ENT doctors, audiologists, physiotherapists and psychiatrists. The ENT doctors and audiologists will examine the presence of possible hearing loss, underlying disorders and tinnitus. The physiotherapists will assess the presence of neck and jaw dysfunctions and the link between these dysfunctions and the tinnitus using the diagnostic criteria for somatic tinnitus [31]. Any active psychiatric disorders, such as anxiety or depression disorders, will be excluded by the psychiatrist. This extensive diagnostic process by a multidisciplinary team is a major strength of our study.

The main scientific risks associated with the present study protocol are insufficient enrolment and patient drop-out. However, every year 2500 patients suffering from tinnitus seek help at the ENT department at UZA. As a quarter of these patients are diagnosed with ST, a maximum of 625 patients will be available for inclusion in our study on an annual basis. Therefore, we expect sufficient enrolment during the inclusion period of 2.5 years. In addition, the willingness of participants to complete the full treatment program and all follow-up tests is crucial for the power of the study results. The risk for drop-out is especially high in patients who do not experience the expected treatment results. To maximise treatment adherence and minimise drop-out, patients will be encouraged to complete the treatment and follow-up phase by the therapist, the study nurse and the researcher. Nonetheless, a drop-out of 10% was considered in the sample size calculation.

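### The primary analysis uses only the baseline-to-1-month TFI change and ignores the TFI taken at the last session and at 3 months, so loss after treatment that differs between arms can bias the non-inferiority comparison in either direction

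*Protocol article*

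**What the plan says.** All points below are from the protocol article.

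- **Endpoint** (Primary outcome measure): "The primary outcome is the change in Tinnitus Functional Index (TFI) score from baseline to 1 month after the treatment".
- **Estimator** (Primary analysis): "After calculating a TFI-change score from baseline to 1-month follow-up, a two-sided 95% confidence interval for the mean difference in this change score" between the arms is compared with the margin of 6.5. No covariate and no other visit is named.
- **Other TFI values.** Outcome measures states: "The following outcome measures will be collected at baseline and during the two follow-up visits". This gives TFI at baseline, 1 month and 3 months. Primary outcome measure continues: "For the cost-effectiveness analysis, an additional time point, immediately after the last treatment session, is added". The purpose given there is to relate the fall in TFI to the EQ-5D-5L.
- **Mixed model** (Secondary analysis): "The continuous secondary outcomes and baseline characteristics, measured at the different time points, will be used in a linear mixed model". It is not assigned to the primary outcome.
- **Analysis sets** (Secondary analysis): "primary and secondary endpoints are analysed in first instance in the per-protocol population". That set holds eligible patients who followed the protocol in full. Intention-to-treat is a later sensitivity analysis, with no separate estimator described.
- **Expected loss.** The Discussion states: "The risk for drop-out is especially high in patients who do not experience the expected treatment results". The Sample size section allows for 10% drop-out overall.

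**The concern.** A change score to 1 month can be calculated only if the 1-month TFI was observed or imputed. Consider a patient who finishes treatment without benefit and then misses the 1-month visit. A last-session TFI showing the poor response may be on file, but the stated primary analysis has no place for it. The protocol predicts that such patients are the likeliest to leave.

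The non-inferiority claim is what is at stake. If more non-responders are lost from one arm, that arm's observed mean change looks better than it is. When that arm is the experimental one, the error is towards a false claim of non-inferiority. When it is the control arm, the test becomes conservative and power is lost.

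The protocol already plans a model that would use the intermediate values, but only for the secondary outcomes.

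**Working it through.** **Inputs from the protocol article.** Margin 6.5; SD 20; one-sided alpha 0.025; power 80%; 150 per group, raised to 167 for 10% drop-out (Sample size and power).

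**Assumptions not in the documents.** SD 20 for the change at both the last session and 1 month. Correlation 0.6 to 0.8 between those two changes. Loss follows a logistic model in the last-session change, with odds multiplied by 2.7 (slope 1) per SD of poorer response. All split rates are assumed.

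**1. The plan's own figure.** The normal approximation for margin 6.5 and SD 20 gives 149 per group. Noncentral-t power is 79.85% at 149 and 80.11% at 150, so 150 is the exact t-test answer. 150 / (1 − 0.10) = 166.7, hence 167. The stated figures reproduce, and nothing below changes them.

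**2. Hand formula for the bias.** Let d be the fraction lost in an arm, and D the amount by which the change in lost patients is worse than in observed patients. The observed mean then looks better than the full mean by d × D. With the same D in both arms:

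bias (experimental minus control, negative favours experimental) = −(dE − dC) × D

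With 15% vs 5% lost and D = 13, the clinically relevant change: −(0.15 − 0.05) × 13 = −1.3. With 10% in each arm: 0.

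**3. Simulation** (400,000 per arm), experimental vs control loss:

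| Loss | Correlation | Bias of change score without imputation | Share of 6.5 |
|---|---|---|---|
| 10% vs 10%, same mechanism | 0.7 | about 0 | about 0 |
| 12% vs 8% | 0.6–0.8 | −0.4 to −0.5 | 6–8% |
| 14% vs 6% | 0.6; 0.8 | −0.83; −1.16 | 13%; 18% |
| 15% vs 5% | 0.6; 0.8 | −1.04; −1.43 | 16%; 22% |
| 10% vs 10%, response-dependent only in experimental | 0.6–0.8 | −1.1 to −1.4 | 17–22% |
| 5% vs 15% | 0.7 | about +1.2 | 18% |
| 15% vs 5%, slope 2 in experimental, 0 in control | 0.7 | −2.8 | 43% |

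**4. Effect on the error rate.** With 150 per group the standard error is 20 × √(2/150) = 2.31. At a true difference of 6.5, the chance of claiming non-inferiority is Φ(−bias/2.31 − 1.96).

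- Bias 0: Φ(−1.96) = 2.5%.
- Bias −0.83: Φ(0.36 − 1.96) = about 5.5%.
- Bias −1.2: Φ(0.52 − 1.96) = about 7.5%.
- Bias −1.43: Φ(0.62 − 1.96) = about 9%.
- Bias +1.2: Φ(−0.52 − 1.96) = about 0.7%.
- Bias −2.8, the most extreme case tried: about 23%.

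**5. Using the last-session TFI.** When every lost patient has a last-session value and loss depends only on it, the estimate that uses it stays within about 0.1 point of the truth in all scenarios. If half of the losses come before the last session, about 0.4 to 0.6 points remain at 14% vs 6% or 15% vs 5%. If three quarters do, 0.7 to 1.0 points remain at 15% vs 5%.

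**The case against.** **No deletion rule is stated.** A reader might infer that every patient without a 1-month TFI is dropped, in the intention-to-treat analysis too. The article does not say so. The 10% inflation and the independent-samples t-test suggest complete cases, but sample-size inflation is a planning convention. Imputation using the other visits could sit in an analysis plan that is not shown, and silence on missing data in an article is not a fault. This stands. What remains is that the stated primary estimator names one visit only, while a model that uses all visits is planned elsewhere in the same section.

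**Bias is not certain, nor is its direction.** A reader might infer a bias favouring the experimental arm. Response-dependent loss alone does not produce this; rates or mechanisms must differ between arms. The documents give one pooled 10%. The experimental arm has six therapist sessions against twelve, and the therapist is one of those who encourage patients to stay, which could raise loss there. Equally, the app is meant to improve compliance and the control arm has the heavier visit load, which could raise loss in control. The objection stands.

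**A new estimator does not rescue the leading analysis.** On its natural reading, the per-protocol set already excludes a patient who misses the 1-month visit, so a mixed model run only there recovers few or none of them. This stands too, and it means the model must also be run in all randomised patients.

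**The size depends on the split.** At 12% vs 8% the bias is 0.4 to 0.5 points, which is modest. Accepted.

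**Conclusion.** The point holds as a choice of a weaker method where a better one is at hand. The protocol expects non-responders to leave and collects TFI values that would help correct for it, but does not use them for the primary contrast. If values are not imputed, the distortion is about 0.8 to 1.4 points (13 to 22% of the margin) under splits of 14% vs 6% or 15% vs 5%. It is smaller for milder imbalance and about zero for equal loss by the same mechanism. Where it favours the experimental arm, the one-sided error of 2.5% rises to about 5.5 to 9% under those splits. The correlation, the loss mechanism and the splits are all assumptions. The documents do not establish that patients are deleted, that bias will occur, or that it will favour the experimental arm.

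**What to change.** In the Primary analysis section, estimate the 1-month difference from a mixed model for repeated measures. It should use all TFI values (baseline, last session, 1 month, 3 months) with an arm-by-time term, and the 95% confidence interval of the 1-month contrast should be compared with 6.5. Apply it in all randomised patients for the intention-to-treat analysis, where it recovers patients lost after the last session, as well as in the per-protocol set. Keep the simple change-score comparison as supportive. Add a sensitivity analysis for departures from missing at random, because the model relies on that assumption.

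The cost is wording plus that extra analysis, fixed before unblinding. The TFI data are already scheduled, the model class is already planned for secondary outcomes, and the endpoint, margin and 150/167 per group stay as they are. The change does not repair loss before the last session.

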### Study design and randomisation procedure

The study is designed as a single-blind two-arm 1:1 randomised controlled trial. After baseline measurements, patients will be randomised into either the experimental group or the control group. A stratified randomisation according to the grade of tinnitus severity obtained by use of the Tinnitus Functional Index (TFI) and gender will be used. The TFI categorises patients from grade 1 (no tinnitus distress) to grade 5 (very severe tinnitus distress) [33–35]. Only grades 2–5 are considered for this study: light distress (7 to 28), moderate distress (29 to 47), severe tinnitus distress (48 to 65) and very severe tinnitus distress (66 to 100) [35]. The stratified randomisation assures an even distribution of patients of each tinnitus grade and of men and women in both treatment arms. A minimisation procedure will be used to perform the stratified randomisation using the web-based online randomisation tool Qminim [36]. Patients will be informed that the study investigates the effectiveness of two different physiotherapy approaches for ST but will not receive in-detail information about the content of the treatment before randomisation. Hence, patients are blinded towards the group they are randomised to. The therapist cannot be blinded. To limit the risk of bias related to lack of blinding of the therapist, all evaluation measurements will be performed by a blinded assessor and data analysts will be blinded as well. An overview of the study design and randomisation procedure is presented in Fig. 1.

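### The primary TFI comparison makes no covariate adjustment for baseline TFI or gender; it is valid at its planned power but less efficient than the data allow

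*Protocol article*

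**What the plan says.** Under Study design and randomisation procedure, the article states: "A stratified randomisation according to the grade of tinnitus severity obtained by use of the Tinnitus Functional Index (TFI) and gender will be used". This is carried out by minimisation.

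Under Sample size and power, the outcome is fixed: "The primary outcome is the change in TFI from baseline to 1-month follow-up". The margin follows: "A non-inferiority margin is chosen at 6.5 points, being half of the minimally clinically important difference". The variability is given as "Assuming a standard deviation of 20 points", without saying whether this is the SD of the change or of a single score. The size of 150 per group is said to give "80% power to show non-inferiority using a one-sided, independent samples" *t*-test, at a significance level of 0.025.

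Under Primary analysis, a change score is calculated and "a two-sided 95% confidence interval for the mean difference in this change score between experimental and control group will be compared" with 6.5. No covariate is named.

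Covariates appear only under Secondary analysis, for the linear mixed models, and as an option: "Other variables such as age, gender and tinnitus grade can also be included in these models".

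**The concern.** Baseline TFI enters the primary analysis only by subtraction, and gender does not enter at all. Subtraction fixes the slope of follow-up on baseline at 1. If the true slope is lower, part of the baseline variation stays in the change score as noise that a covariate would remove. In addition, minimisation makes the arms more alike on TFI grade and gender than simple randomisation would, but an interval that leaves those factors out takes no credit for this, so its standard error tends to be too large.

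In a non-inferiority trial a wider interval works against the experimental arm: a programme that is truly no worse is more likely to have an upper limit beyond 6.5. At stake is power that could be had from data already being collected.

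**Working it through.** **Inputs from the article.** Margin 6.5; SD 20; one-sided 0.025, equivalent to a two-sided 95% interval; 150 evaluable per group; 10% drop-out; 1:1 allocation. A true difference of 0 is read from the hypothesis of no difference between groups.

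**Assumed.** The correlation rho between baseline and 1-month TFI is not given, so a range is shown. The only related figure is the test-retest value of 0.78 under Primary outcome measure, which is plausibly an upper value across a treatment period.

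**1. The plan's own figure.** n = 2 × SD² × (z₀.₉₇₅ + z₀.₈₀)² / margin² = 2 × 400 × (1.960 + 0.842)² / 42.25 ≈ 148.6, so 149 per group. The noncentral *t* version gives 150, with power 80.1%. Then 150 / 0.90 = 166.7, so 167 per group and 334 in total. All three figures reproduce.

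**2. Baseline adjustment, SD 20 taken as the SD of the change, equal variances.** With score variance σ², Var(change) = 2σ²(1 − rho) and the ANCOVA residual variance is σ²(1 − rho²). The ratio is (1 + rho)/2, so the working SD is 20 × √((1 + rho)/2). The half-width is 1.96 × SD × √(2/150).

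| rho | SD | Power at 150 per group | 95% half-width | n per group for 80% (normal approximation) |
|---|---|---|---|---|
| unadjusted | 20.00 | 80.1% | 4.53 | 149 |
| 0.5 | 17.32 | 90.0% | 3.92 | 112 |
| 0.6 | 17.89 | 88.0% | 4.05 | 119 |
| 0.78 | 18.87 | 84.5% | 4.27 | 133 |
| 0.9 | 19.49 | 82.1% | 4.41 | 142 |

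**3. With minimisation simulated.** There were 3,000 runs per setting. Allocation was biased-coin minimisation (probability 0.8, an assumption) on TFI grade and sex, scores were normal, and the adjusted model used continuous baseline TFI and sex.

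| rho | Power, unadjusted | Power, adjusted | One-sided type I error, unadjusted | One-sided type I error, adjusted |
|---|---|---|---|---|
| 0.5 | 82.5% | 89.9% | 1.2% | 2.0% |
| 0.6 | 83.1% | 88.8% | 1.4% | 2.2% |
| 0.78 | 81.2% | 84.5% | 2.2% | 2.6% |

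Simulation error is about 0.7 points for power and 0.3 points for type I error. The power gains are 7.4, 5.7 and 3.3 points. They are smaller than in step 2 because minimisation already helps the unadjusted estimate. Against a nominal 2.5%, the unadjusted interval is clearly conservative at rho 0.5 and 0.6. At 0.78 the departure is within simulation error.

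**4. Unequal variances.** Let k be the follow-up SD divided by the baseline SD. The variance ratio is k²(1 − rho²) / (1 + k² − 2 × rho × k). At rho 0.78 and k = 1.2 this is 1.44 × 0.3916 / (1 + 1.44 − 1.872) = 0.564 / 0.568 = 0.99. The slope is 0.78 × 1.2 = 0.94, close to the 1 that subtraction assumes, so almost nothing is gained.

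**5. SD 20 taken as the SD of a single score.** The change SD is 20 × √(2(1 − rho)) and the ANCOVA SD is 20 × √(1 − rho²).

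| rho | Change SD | ANCOVA SD | Power, unadjusted | Power, adjusted |
|---|---|---|---|---|
| 0.3 | 23.66 | 19.08 | 66.0% | 83.7% |
| 0.5 | 20.00 | 17.32 | 80.1% | 90.0% |
| 0.78 | 13.27 | 12.52 | 98.8% | 99.4% |

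**The case against.** The sample-size and primary-analysis sections agree with each other, the numbers reproduce, and the unadjusted interval errs on the cautious side. On this view nothing is wrong; a more efficient method merely exists. A *t*-test sizing does not rule out an adjusted analysis, and covariate lists are often left to the analysis plan. The size of the gain also rests on a correlation that the documents do not give.

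Most of this stands as a limit on size, not as a reason to drop the point. The article does more than stay silent: it names the estimator, sizes the trial on the unadjusted test, and mentions covariates only for the secondary models. If covariates were added later without a prespecified change, the choice could look data-driven.

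Several stronger readings are tempting but not supported:

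- *The analysis ignores baseline TFI.* It uses baseline by subtraction; what it lacks is adjustment for baseline as a covariate.
- *The trial is underpowered, or false non-inferiority is more likely.* With the stated SD of 20 applied to the change, the planned 80% is reached, and simulated type I error for the unadjusted interval does not exceed 2.5%.
- *A change score over-corrects whenever rho is below 1.* That needs equal variances. In general the condition is that the slope, rho times the ratio of follow-up to baseline SD, is below 1.
- *Adjustment is worth about 10 points of power.* That figure needs rho 0.5 and leaves out what minimisation already contributes.
- *The scale floor makes baseline a strong predictor of change.* A patient entering at 7 can indeed fall by at most 7 points, but no baseline distribution is given, so the strength of this effect is unknown.
- *Chance imbalance in baseline TFI is a material problem.* Minimisation limits imbalance between grades, and the documents give no basis for sizing what remains.

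**Conclusion.** The point holds as one of efficiency. The primary analysis is valid and meets its planned power, but it leaves unused a baseline covariate and an allocation factor that are already recorded. Its interval also tends to be conservative after minimisation, mainly at lower rho.

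The best estimate of the cost under this design is about 3 to 7 points of power for rho from 0.78 to 0.5, assuming equal variances, an SD of 20 for the change, and the minimisation settings simulated. The gain is about 2 points by formula at rho 0.9, close to nil where the follow-up SD is enough above the baseline SD to bring the slope near 1, and 0.6 points if 20 is a single-score SD and rho is 0.78. Neither rho nor the meaning of the SD can be settled from the documents. The change is worth making because it costs almost nothing, not because the trial fails without it.

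**What to change.** Before the blind is broken, amend Primary analysis and carry the same wording into the analysis plan. The primary estimate becomes the experimental-minus-control difference in 1-month TFI from an ANCOVA with treatment arm, continuous baseline TFI and gender. Non-inferiority is concluded if the upper limit of the two-sided 95% interval lies below +6.5. Using the change score as the response in the same model gives the identical treatment estimate, so the stated outcome can stay. Continuous baseline TFI carries the information in the TFI grade, which is a grouping of it.

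Keep the unadjusted change-score interval as a supportive analysis. It would also help to state whether the SD of 20 refers to the change or to a single score.

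The cost is a sentence or two of text. Margin, sample size and data collection do not change.
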